## 5.4 Sensitivity Estimand for the Key Secondary Endpoints

The first sensitivity estimand will include data from participants in the target population of the key secondary estimand plus data collected after the withdrawal of study treatment through Week 12 from

participants who discontinue study treatments prior to Week 12 for reasons other than lack of efficacy or response.

| Attribute                                          | Details                                                                                                                                                                                                                                                                                                                                                                                                                                                                                                                                                                                                                                                                                                                                                                                                                                                                                                                                                                                                                                                                                                           |
|----------------------------------------------------|-------------------------------------------------------------------------------------------------------------------------------------------------------------------------------------------------------------------------------------------------------------------------------------------------------------------------------------------------------------------------------------------------------------------------------------------------------------------------------------------------------------------------------------------------------------------------------------------------------------------------------------------------------------------------------------------------------------------------------------------------------------------------------------------------------------------------------------------------------------------------------------------------------------------------------------------------------------------------------------------------------------------------------------------------------------------------------------------------------------------|
| Treatments                                         | 
Sonelokimab at 3 different doses:
 
 
• sonelokimab 120 mg Q2W or
 
• sonelokimab 60 mg Q2W or
 
• sonelokimab 60 mg Q4W
 
                                                                                                                                                                                                                                                                                                                                                                                                                                                                                                                                                                                                                                                                                                                                                                                                                                                                                                                       |
| Target Population                                  | 
 
• Adults with a confirmed diagnosis of PsA per the 2006 CASPAR [Taylor W. et al., 2006] with symptoms for <math>\geq 6</math> months prior to the Screening Visit;
 
• Analysis Set: FAS
 
                                                                                                                                                                                                                                                                                                                                                                                                                                                                                                                                                                                                                                                                                                                                                                                                                                                 |
| Endpoint                                           | 
The key secondary endpoints are as follows:
 
 
• ACR20 response rate at Week 12 compared with baseline;
 
• PASI90 at Week 12 compared with baseline in the subgroup of participants with PsO involving at least 3% BSA at baseline.
 
                                                                                                                                                                                                                                                                                                                                                                                                                                                                                                                                                                                                                                                                                                                                                                                                                 |
| Intercurrent events and strategies to handle those | 
 
• Use of prohibited concomitant medication (Section 10.5.1 of protocol): participants will be analyzed as a treatment failure after taking prohibited medication, i.e., non-responder imputation will be performed after the first episode of prohibited medication for all future assessments (composite strategy);
 
• Withdrawal from treatment due to lack of efficacy or adverse event (Section 9.6 of protocol): participants will be considered non-responders to treatment if they discontinue the study prior to the Week 12 visit (composite strategy);
 
• Withdrawal from treatment due to any reason other than lack of efficacy or adverse event (Section 9.6 of protocol): participants will continue to be followed and use their observed Week 12 Visit (treatment policy strategy). Any missing data for participants who do not have a Week 12 visit will be assumed to be missing at random;
 
• Study treatment non-adherence (missing doses) or drug administration error: participants will be analyzed in the same
 
 |

|  |                                                                      |
|--|----------------------------------------------------------------------|
|  | way as if the event had occurred or not (treatment policy strategy). |
|--|----------------------------------------------------------------------|

The second sensitivity estimand will include data from participants in the target population of the primary estimand targeting the treatment policy estimand such that the difference in response between treatments are analysed regardless of prohibited medication and withdrawal from treatment.

| Attribute                                          | Details                                                                                                                                                                                                                                                                                                                                                                                                                                                                                                                                                                                                                                                                                                                                                                                 |
|----------------------------------------------------|-----------------------------------------------------------------------------------------------------------------------------------------------------------------------------------------------------------------------------------------------------------------------------------------------------------------------------------------------------------------------------------------------------------------------------------------------------------------------------------------------------------------------------------------------------------------------------------------------------------------------------------------------------------------------------------------------------------------------------------------------------------------------------------------|
| Treatments                                         | 
Sonelokimab at 3 different doses:
 
 
• sonelokimab 120 mg Q2W or
 
• sonelokimab 60 mg Q2W or
 
• sonelokimab 60 mg Q4W
 
                                                                                                                                                                                                                                                                                                                                                                                                                                                                                                                                                                                             |
| Target Population                                  | 
 
• Adults with a confirmed diagnosis of PsA per the 2006 CASPAR [Taylor W. et al., 2006] with symptoms for <math>\geq 6</math> months prior to the Screening Visit
 
• Analysis Set: Full Analysis Set (FAS)
 
                                                                                                                                                                                                                                                                                                                                                                                                                                                                                                    |
| Endpoint                                           | 
The key secondary endpoints are as follows:
 
 
– ACR20 response rate at Week 12 compared with baseline;
 
– PASI90 at Week 12 compared with baseline in the subgroup of participants with PsO involving at least 3% BSA at baseline.
 
                                                                                                                                                                                                                                                                                                                                                                                                                                                                                       |
| Intercurrent events and strategies to handle those | 
 
• Use of prohibited concomitant medication (Section 10.5.1 of protocol): observed data after taking prohibited medication will be used in the analysis (treatment policy strategy); Any missing data for participants who do not have a Week 12 visit will be assumed to be missing at random;
 
• Withdrawal from treatment for any reason (Section 9.6 of protocol): participants will continue to be followed and use their observed Week 12 Visit (treatment policy strategy). Any missing data for participants who do not have a Week 12 visit will be assumed to be missing at random;
 
• Study treatment non-adherence (missing doses) or drug administration error: participants will be analyzed in the same
 
 |

|  |                                                                      |
|--|----------------------------------------------------------------------|
|  | way as if the event had occurred or not (treatment policy strategy). |
|--|----------------------------------------------------------------------|

5.5 Sample Size and power

The sample size calculation is based on the primary efficacy endpoint (i.e., ACR50 response rate at Week 12 compared with baseline) with the primary comparisons of interest being:

sonelokimab 120 mg Q2W (Arm 1) vs placebo (Arm 4), sonelokimab 60 mg Q2W (Arm 2) vs placebo (Arm 4) and sonelokimab 60 mg Q4W (Arm 3) vs placebo (Arm 4) and determined based on assumed ACR50 response rates as follows:

- 40% with each sonelokimab dose regimen;
- 10% with placebo.

The estimated response rates for sample size were based on past IL-17 inhibitors for the treatment of participants with PsA. The Cosentyx FUTURE 2 study showed that ACR50 was achieved in 35% of secukinumab 300 mg and 37% of secukinumab 150 mg, vs 6% in the placebo arm [McInnes I.B. et al., 2015].

A sample size of n = 40 participants in each of the sonelokimab 120 mg Q2W, sonelokimab 60 mg Q2W, sonelokimab 60 mg Q4W and placebo arms (therefore, 160 participants in total) results in a power of more than 80%, while assuming an overall 2-sided alpha of 0.025, a placebo ACR50 response rate of 10% and a difference in ACR50 response rate of 30% between placebo and each sonelokimab dose regimen. An additional 40 participants will be randomized in the adalimumab arm. The adalimumab treatment will be used as an active reference arm, however, no formal comparison of sonelokimab or placebo vs adalimumab is planned.

Eligible participants will be randomized in a 1:1:1:1:1 ratio to sonelokimab 120 mg Q2W (Arm 1), sonelokimab 60 mg Q2W (Arm 2), sonelokimab 60 mg Q4W (Arm 3), placebo (Arm 4) or adalimumab 40 mg Q2W (Arm 5). The total proportion of participants with previous use of biologic agents will be capped at 30%.

Due to the use of the FAS with non-responder imputation, no accounting for dropout is required, therefore a total of approximately 200 participants will be randomized.

All calculations were performed in nQuery® Software version 8.5.1.0.

## **6 ANALYSIS POPULATIONS**

### **6.1 Part A**

#### **6.1.1 Enrolled Set**

The enrolled set is defined as all participants who signed an informed consent.

#### **6.1.2 Safety Analysis Set (SAF)**

The safety analysis set (SAF) is defined as all randomized participants who received at least one dose of study treatment. Participants will be analyzed based on the treatment that they actually received, regardless of the treatment they are randomized to.

The SAF will be used for all safety analyses related to the Part A and Part A+B.

#### **6.1.3 Full Analysis Set (FAS)**

The FAS is defined as all randomized participants. Participants will be analyzed in accordance with the intention-to-treat (ITT) principle, i.e., based on randomized treatment, irrespective of the treatment they actually received.

The FAS will be used for all efficacy analyses on efficacy endpoints related to the Part A and some Part A+B analyses and will serve as the primary analysis set.

#### **6.1.4 Immunogenicity Analysis Set (IG Analysis Set)**

The IG analysis set is defined as all participants who received at least one dose of sonelokimab and who have at least 1 sample obtained for the detection of antibodies to sonelokimab.

In the IG analyses, participants will be analyzed according to the treatment they actually received, regardless of the treatment they are randomized to.

The IG analysis set will be used for all immunogenicity analyses related to the Part A and A+B.

#### **6.1.5 Pharmacokinetic Analysis Set (PK Analysis Set)**

The PK analysis set is defined as all participants who received at least one complete dose of sonelokimab and had at least 1 valid blood sample drawn for PK analysis after their first dose of sonelokimab.

In the PK analyses, participants will be analyzed according to the treatment they actually received, regardless of the treatments they are randomized to.

The PK analysis set will be used for all PK analyses related to the Part A and A+B.

### **6.2 Part B**

#### **6.2.1 Safety Analysis Set (SAF-B)**

The SAF-B is defined as all randomized participants who received at least one dose of study treatment during Part B. Participants will be analyzed based on the treatment that they actually received, regardless of the treatments they are randomized to.

The SAF-B will be used for all safety analyses related to Part B.

## 6.2.2 Full Analysis Set (FAS-B)

The FAS-B is defined as all randomized participants who are assigned treatment for Part B. Participants will be analyzed in according to the intention-to-treat principle, i.e., based on assigned treatment for Part B, irrespective of the treatment they actually received. The FAS-B will be used for some efficacy analyses on endpoints related to the Part B.

## 6.3 Protocol Deviations/Violations and Exclusions from Analysis Sets

All protocol deviations will be identified prior to their associated database lock for any intentional or unintentional change or noncompliance with the approved protocol procedures or requirements as mentioned in protocol deviation criteria form (PDCF).

All protocol deviations will be classified as key or non-key and will be reviewed to determine their impact on the primary and key secondary endpoints during a data review meeting.

All exclusions from an analysis population will be documented prior to unblinding, exceptions to this will be protocol deviations based upon unblinded data (e.g PK analysis set) which will documented prior to release of the final outputs.

## 7 STATISTICAL CONSIDERATIONS AND ANALYSIS

### 7.1 Derived Variables

The below table provides the list of derived variables for demographic and baseline characteristics, various duration derivations, drug compliance, baseline derivations and other important derivations applicable for this study.

| Variables                                       | Formula                                                                                                                                                                                                                                                                                                                                         |
|-------------------------------------------------|-------------------------------------------------------------------------------------------------------------------------------------------------------------------------------------------------------------------------------------------------------------------------------------------------------------------------------------------------|
| Demographic and Baseline Characteristics |                                                                                                                                                                                                                                                                                                                                                 |
| Body mass index (BMI) (kg/m  )      | weight (kg)/[height (m)  ]
Note: 1 lbs = 0.45359237 kg
1 in = 2.54 cm                                                                                                                                                                                                                                                         |
| Duration of PsA (Year)                          | [(Date of first study drug administration – Date of Initial diagnosis) + 1]/ 365.25
Details for imputing missing or partial start and/or stop dates of PsA are described in Section 7.3.2 .                                                                                                                                  |
| Derivation of Duration                   |                                                                                                                                                                                                                                                                                                                                                 |
| Study day at any visit                          | Date of interest – date of first dose of study drug. One day is added if this difference is $\geq 0$ .                                                                                                                                                                                                                                          |
| Duration of Exposure (Days) for Part A          | Date of Week 12 or EOT visit, whichever occurs first – Date of first randomized study medication intake at baseline + 1.                                                                                                                                                                                                                        |
| Duration of Exposure (Days) for Part B          | Date of Week 24 or EOT visit, whichever occurs first – Date of first study medication intake for Part B + 1                                                                                                                                                                                                                                     |
| Duration of Exposure (Days) for Part A+B        | Date of Week 24 or EOT visit, whichever occurs first – Date of first sonelokimab intake + 1                                                                                                                                                                                                                                                     |
| Drug Compliance                          |                                                                                                                                                                                                                                                                                                                                                 |
| Compliance                                      | Compliance (%) = 100 * (number of visits with treatment received/ number of visits with treatment planned) during the participant's participation in the study.
Compliance is calculated for Part A, Part B and Part A+B using the number of visits with treatment received during the respective Part and planned number in each Part also. |
| Baseline Derivations                     |                                                                                                                                                                                                                                                                                                                                                 |
| Baseline definition                             | Baseline will be defined as the last non-missing measurement prior to first dose of study medication in Part A For baseline characteristics table, if a subject is randomized and not treated then the latest record will be defined as the baseline.                                                                                           |
| Baseline definition for ADA                     | The last sample prior to the first dose of sonelokimab                                                                                                                                                                                                                                                                                          |

|                                                                                                        |                                                          |
|--------------------------------------------------------------------------------------------------------|----------------------------------------------------------|
| Change from baseline                                                                                   | The value at each time point minus the value at baseline |
| Other Derivations                                                                               |                                                          |
| Definition for the derived efficacy parameters are given in the respective efficacy analysis sections. |                                                          |

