**Table 1: Treatment Allocation in Part A+B**

| Treatment Assignment in Part A | Treatment Allocation in Part B (Based Upon Response at Week 12) |                        |
|--------------------------------|-----------------------------------------------------------------|------------------------|
|                                | Responder                                                       | Non-responder          |
| Arm 1: Sonelokimab 120 mg Q2W  | Sonelokimab 120 mg Q4W                                          | Adalimumab 40 mg Q2W   |
| Arm 2: Sonelokimab 60 mg Q2W   | Sonelokimab 60 mg Q4W                                           | Sonelokimab 120 mg Q4W |
| Arm 3: Sonelokimab 60 mg Q4W   | Sonelokimab 60 mg Q4W                                           | Sonelokimab 120 mg Q4W |
| Arm 4: Placebo                 | Sonelokimab 120 mg Q4W                                          | Sonelokimab 120 mg Q4W |
| Arm 5: Adalimumab 40 mg Q2W    | Adalimumab 40 mg Q2W                                            | Sonelokimab 120 mg Q2W |

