### 3.3.1 Sonelokimab

Sonelokimab drug product is supplied as a fixed-dose, prefilled syringe to be administered via subcutaneous (SC) injection. Syringes and cartons will be supplied in a blinded manner.

Sonelokimab will be administered by a site-approved, study treatment administrator, who is unblinded. Blinded study personnel will not be in attendance while study treatment is being prepared or administered.

In Part A, the 3 sonelokimab treatment arms are as follows:

- Arm 1 (sonelokimab 120 mg Q2W): Sonelokimab 120 mg will be given as SC injection at Weeks 0, 2, 4, 6 and 8. Participants will receive a placebo injection at Week 10 to maintain the blind;
- Arm 2 (sonelokimab 60 mg Q2W): Sonelokimab 60 mg will be given as SC injection at Weeks 0, 2, 4, 6 and 8. Participants will receive a placebo injection at Week 10 to maintain the blind;
- Arm 3 (sonelokimab 60 mg Q4W): Sonelokimab 60 mg will be given as SC injection at Weeks 0, 4 and 8. Participants will receive a placebo injection at Weeks 2, 6 and 10 to maintain the blind.

In Part B, after allocation of responders and non-responders, the sonelokimab treatment arms are as follows:

- Responders from Arm 1, non-responders from Arm 2, non-responders from Arm 3, and participants from Arm 4 will receive sonelokimab 120 mg Q4W until Week 20. Placebo injections will be given at Weeks 14, 18, and 22 to maintain the blind;
- Responders from Arm 2 and responders from Arm 3 will receive sonelokimab 60 mg Q4W until Week 20. Placebo injections will be given at Weeks 14, 18, and 22 to maintain the blind;

- Non-responders in Arm 5 will receive sonelokimab 120 mg Q2W with SC injections at Weeks 12, 14, 16, 18, and 20. Participants will receive a placebo injection at Week 22 to maintain the blind.

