### 3.3.3 Adalimumab

Adalimumab will be provided in prefilled syringes (40 mg) as sterile solution for SC injection. Adalimumab syringes will be relabelled and repackaged to facilitate maintenance of the study blinding.

Adalimumab will be administered by a site-approved, study treatment administrator, who is unblinded. Blinded study personnel will not be in attendance while study treatment is being prepared or administered.

During Part A, for participants randomized to Arm 5, adalimumab will be given as 40 mg SC every 2 weeks, with injections at Weeks 0, 2, 4, 6, 8 and 10 in accordance with the approved labelling.

In Part B, non-responders from Arm 1 and responders from Arm 5 will receive adalimumab 40 mg Q2W administered by SC injection at Weeks 12, 14, 16, 18, 20, and 22.

A detailed description of procedures and assessments to be conducted during this study is summarized in the Schedule of Activities (SOA) in Table 1 of the protocol.

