## 8.5 Extent of Exposure

Extent of exposure will be listed and summarized using the SAF separately for Part A and Part A+B and SAF-B for Part B.

For Part A+B, only two groups will be presented:

- Sonelokimab 120 mg,
- Sonelokimab 60 mg.

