### 8.5.1 Treatment Duration

The duration (days) ([Section 7.1](#) for derivations) of exposure to study drug will be summarized using descriptive statistics by treatment group. In addition, the number of injections received will be summarized with count and percentages.

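### Part A+B exposure is derived without a stop at the Week 12 treatment change but tabulated by sonelokimab dose, so switchers' time is credited to the wrong dose or the wrong drug

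*Combined protocol and SAP*

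**What the plan says.** SAP 7.1 gives three exposure durations.

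- Part A: "Date of Week 12 or EOT visit, whichever occurs first – Date of first randomized study medication intake at baseline + 1".
- Part B: "Date of Week 24 or EOT visit, whichever occurs first – Date of first study medication intake for Part B + 1".
- Part A+B: "Date of Week 24 or EOT visit, whichever occurs first – Date of first sonelokimab intake + 1".

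SAP 8.5 then states "For Part A+B, only two groups will be presented", namely sonelokimab 120 mg and sonelokimab 60 mg. SAP 8.5.1 says that the duration "of exposure to study drug will be summarized using descriptive statistics by treatment group" and refers back to 7.1. No other derivation is given.

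Treatment can change at Week 12. SAP 3.3.1 says: "Responders from Arm 1, non-responders from Arm 2, non-responders from Arm 3, and participants from Arm 4 will receive sonelokimab 120 mg Q4W". SAP 3.3.3 says: "In Part B, non-responders from Arm 1 and responders from Arm 5 will receive adalimumab 40 mg Q2W". Non-responders in Arms 2 and 3 therefore move from 60 mg to "Sonelokimab 120 mg Q4W" (SAP Table 1), and non-responders in Arm 1 leave sonelokimab.

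For the Part A+B total groups, SAP 8.1 shows a participant's results only for the Part in which the relevant treatment was taken. SAP 8.9 applies a similar limit to summary visits. SAP 8.1 also confines Part A+B tables to adverse events, which does not fit the Part A+B exposure table planned in 8.5.

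**The concern.** The Part A+B duration is one number per participant, running from the first sonelokimab dose to the end of treatment. The table that reports it is by dose, and the design moves participants between doses and, in Arm 1, off the drug. SAP 8.5 says neither which group a switcher enters nor how the time is divided. Followed literally, the full duration goes to whichever group or groups the switcher is placed in.

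Extent of exposure by dose is the background for reading the 60 mg and 120 mg safety data. The adverse event tables with the same dose labels divide each participant's experience by Part, so the two sets of tables would describe different time. Two programmers could also follow the text and produce different tables.

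**Working it through.** The documents state no exposure total, so there is no planned figure to reproduce. The check applies the SAP's own formulas to the scheduled days.

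**Inputs.** First dose Day 1, Week 12 Day 85, Week 24 Day 169 (protocol Table 1; SAP 7.2). Planned 40 per arm (SAP 5.5). The share of non-responders is not given, so 10% to 50% is assumed.

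**One participant, 60 mg to 120 mg, treated to Week 24.**
- Part A+B formula: 169 - 1 + 1 = 169 days.
- Time at 60 mg (Part A formula): 85 - 1 + 1 = 85 days.
- Time at 120 mg (Part B formula): 169 - 85 + 1 = 85 days.
- Ratio: 169/85 = 1.99. Day 85 falls in both Parts; counted once, the split is 84 + 85 = 169.

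Counted in both groups, this participant is credited with 2 × 169 = 338 days for 169 days on drug.

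**Arm 1 non-responder treated to Week 24.** The formula again gives 169 days. Sonelokimab ran for 85 by the Part A formula; the rest is adalimumab.

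**Switcher stopping in Part B.** With EOT at Week 16 (Day 113) the formula gives 113 days, against 85 at 60 mg (1.33 times) and 113 - 85 + 1 = 29 at 120 mg (3.9 times). With EOT at Week 20 (Day 141) it gives 141, against 85 (1.66 times) and 57 (2.5 times).

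**Group totals.** These assume 40 per arm, no dropout, no US participants, and the same non-responder share q in Arms 1, 2, 3 and 5.
- 60 mg, time at dose: 80 × [(1 - q) × 169 + q × 85]. Formula with switchers under 60 mg: 80 × 169 = 13,520.
- 120 mg, time at dose: 40 × [(1 - q) × 169 + q × 85] for Arm 1, plus 80q × 85 for Arm 2 and 3 switchers, 40 × 85 for placebo, and 40q × 85 for Arm 5 non-responders.
- 120 mg, formula, switchers in both groups: 40 × 169 + 80q × 169 + 40 × 85 + 40q × 85. With switchers under their first dose only, the 80q × 169 term drops out.

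| q | 60 mg at dose | 60 mg by formula | 120 mg at dose | 120 mg by formula, both groups | 120 mg by formula, first dose only |
|---|---|---|---|---|---|
| 10% | 12,848 | 13,520 (+5%) | 10,844 | 11,852 (+9%) | 10,500 (-3%) |
| 20% | 12,176 | 13,520 (+11%) | 11,528 | 13,544 (+17%) | 10,840 (-6%) |
| 30% | 11,504 | 13,520 (+18%) | 12,212 | 15,236 (+25%) | 11,180 (-8%) |
| 50% | 10,160 | 13,520 (+33%) | 13,580 | 18,620 (+37%) | 11,860 (-13%) |

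Counting Day 85 once, the 60 mg figure at q = 50% is 80 × 84 + 40 × 85 = 10,120, and 13,520/10,120 = 1.34. Both 120 mg formula columns include the adalimumab time of Arm 1 non-responders.

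**Not affected.** Participants who stay at one dose level (169 days, correct), those starting sonelokimab at Week 12 after placebo or adalimumab (85 days, correct), and US participants, who stop at Week 12.

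**The case against.** The strongest reply is that SAP 8.1, the general conventions section, already limits Part A+B total groups to the Part in which the treatment was taken. A programmer could combine that rule with the separate Part A and Part B durations in 7.1 and divide a switcher's time correctly. That is probably the intention, but the text does not get there. SAP 8.1 confines Part A+B tables to adverse events, the 8.9 limit concerns summary visits rather than a single duration, and neither changes the 7.1 formula to which 8.5.1 points.

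Other parts of the reply stand. Exposure is also summarized separately for Part A and Part B, and the Part B groups follow the full treatment sequence, so correct time at each dose can be seen elsewhere. The non-responder shares are assumptions, and 50% may be high: protocol 8.9 cites ACR20 response of 51% to 54% for another IL-17 inhibitor at Week 24, and the joint-count criterion used here is easier to meet than ACR20. On that reference non-response would be at most 46% to 49%.

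A reader might infer that exposure at both doses is simply doubled. The documents do not support that. The factor near 2 belongs to individual switchers treated to Week 24, group totals move far less, and the 120 mg total can fall short. A reader might also infer that the exposure-adjusted adverse event rates inherit the error. They do not use the 7.1 duration: Appendix K defines its own observation period. That period also runs through Part B without a split for participants randomized to sonelokimab, but that is a separate matter.

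**Conclusion.** The point holds. Followed as written, SAP 7.1 and 8.5 give a wrong dose-level exposure for anyone whose treatment changes at Week 12 from a sonelokimab arm, so this is more than a missing detail.

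For switchers treated to Week 24 the individual error is certain from the schedule. The group-level error is conditional: 60 mg is about 5% to 33-34% too high if switchers sit under 60 mg; 120 mg is 9% to 37% too high if they count in both groups, or 3% to 13% too low if they count only under their first dose. Those ranges rest on assumed non-responder shares of 10% to 50%, 40 per arm, no dropout and no US participants.

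The consequence is confined to one descriptive safety table. Efficacy, hypothesis testing and the separate Part A and Part B exposure tables are unaffected. It should be corrected because the correction is cheap and the table is read alongside the dose-level safety data.

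**What to change.** 1. In SAP 7.1, derive Part A+B exposure per sonelokimab dose level as the sum of the existing Part A and Part B durations over only the Parts in which the participant was assigned that dose. For participants staying at the same dose level, count the Week 12 day once (85 + 85 - 1 = 169).
2. Exclude time on adalimumab, so that Arm 1 non-responders contribute Part A only.
3. In SAP 8.5, state that switchers contribute to each dose group only for the relevant Part, as in 8.1 and 8.9.
4. Reconcile 8.5 with the statement in 8.1 that Part A+B tables are for adverse events only.

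The cost is one derivation and a few sentences of SAP text. All the dates needed are already collected, and the result will agree with the Part A and Part B exposure tables.
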